### Adverse events (AE), adverse reactions (AR), and safety issues

#### Definition of AE

Any untoward medical occurrence in a patient or clinical investigation participant administered a medicinal product, which does not necessarily X have a causal relationship with this treatment (the study medication). An AE can therefore be any unfavorable and unintended sign (including an abnormal laboratory finding), symptom or disease temporarily associated with the use of the study medication/procedure, whether or not considered related to the study medication.

#### Definition of AR

All untoward and unintended responses to a medicinal product related to any dosage. "Responses to a medicinal product" means that a causal relationship between a study medication and an AE is at least a reasonable possibility, i.e., the relationship cannot be ruled out. All cases judged by either the reporting medically qualified professional or the sponsor as having a reasonable suspected causal relationship to the study medication/procedure qualify as adverse reactions.

#### Definition of Serious Adverse Event (SAE)

A serious adverse event is any untoward medical occurrence that at any dosage, results in: death, any life-threatening event, any event requiring hospitalization or prolongation of actual hospitalization, any event resulting in persistent or significant disability/incapacity, the occurrence of a congenital anomaly/birth defect, or other important medical event (other events that may not result in death are not life threatening, or do not require hospitalization, may be considered a serious adverse event when, based upon appropriate medical judgment, the event may jeopardize the patient and may require medical or surgical intervention to prevent one of the outcomes listed above.

To ensure no confusion or misunderstanding of the difference between the terms "serious" and "severe", which are not synonymous, the following note of clarification is provided

The term "severe" is often used to describe the intensity (severity) of a specific event (as in mild, moderate, or severe myocardial infarction); the event itself, however, may be of relatively minor medical significance (such as severe headache).

#### Definition of Serious Adverse Reaction (SAR)

An adverse event (expected or unexpected) that is both serious and, in the opinion of the reporting investigator, believed with reasonable probability to be due to one of the study treatments, based on the information provided.

#### Definition of Suspected Unexpected Serious Adverse Reaction (SUSAR)

A serious adverse reaction, the nature or severity of which is not consistent with the applicable product information (e.g. Investigator's Brochure for an unapproved investigational product or summary of product characteristics for an approved product).

#### Causality and expectedness

The relationship of each adverse event to the trial medication will be determined by a medically qualified clinician according to the following definitions

#### Related

The adverse event follows a reasonable temporal sequence from trial medication administration. It cannot reasonably be attributed to any other cause.

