#### Not related

The adverse event is probably produced by the participant's clinical state or by other modes of therapy administered to the participant.

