#### Procedures for recording AE

All AEs occurring during the study/or until observed by the investigator or reported by the participant, whether or not attributed to study medication, will be recorded on the CRF. The following information will be recorded: description, date of onset and end date, severity, assessment of relatedness to study medication, other suspect drug or device and action taken. Follow-up information should be provided as necessary.

AEs considered related to the study medication as judged by a medically qualified investigator or the sponsor will be followed until resolution or the event is considered stable. All related AEs that result in a participant's withdrawal from the study or are present at the end of the study, should be followed up until a satisfactory resolution occurs. It will be left to the investigator's clinical judgment whether or not an AE is of sufficient severity to require the participant's removal from treatment. A participant may also voluntarily withdraw from treatment due to what he or she perceives as an intolerable AE. If either of these occurs, the participant must undergo an end of study assessment and be given appropriate care under medical supervision until symptoms cease or the condition becomes stable.

The relationship of AEs to the study medication will be assessed by a medically qualified investigator.

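### The protocol judges causality of adverse events by three conflicting thresholds, and its 'related' and 'not related' categories leave some events in neither

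*Protocol article*

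**What the plan says.** Four places in the safety part of the protocol article set a causality test.

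- *Definition of AR*: an event counts as an adverse reaction when "a causal relationship between a study medication and an AE is at least a reasonable possibility, i.e., the relationship cannot be ruled out". Either the reporting professional or the sponsor may make that judgement.
- *Definition of Serious Adverse Reaction (SAR)*: the event must be serious and, in the reporting investigator's opinion, "believed with reasonable probability to be due to one of the study treatments". The SUSAR definition builds on this one.
- *Related*: a first sentence deals with timing, "The adverse event follows a reasonable temporal sequence from trial medication administration", and a second one excludes other explanations, "It cannot reasonably be attributed to any other cause", without any qualification.
- *Not related*: here the test is whether some other cause is probable, in the words "The adverse event is probably produced by the participant's clinical state or by other modes of therapy administered to the participant".

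The text under *Causality and expectedness* makes the last two definitions the ones the clinician applies to each adverse event. Under *Procedures for recording AE*, relatedness is one of the items entered on the CRF. The same section gives an explicit commitment that depends on it: "AEs considered related to the study medication as judged by a medically qualified investigator or the sponsor will be followed until resolution". Stabilisation also ends this follow-up.

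**The concern.** The adverse reaction definition asks whether the drug can be excluded as a cause. The operative rule for 'related' asks whether everything else can be excluded. These tests point in nearly opposite directions, and an assessor cannot satisfy both.

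The population makes this more than a drafting slip. Patients are 65 or older, have a hip fracture and undergo surgery. The safety endpoints listed under *Outcome measures* include thrombosis, arterial embolism, cerebrovascular accidents, acute coronary syndrome, heart failure and infections. For many of these, the fracture, the operation, immobility or age is a reasonable alternative cause. Safety is a stated objective of the trial, and the classes of adverse reaction, serious adverse reaction and SUSAR all rest on a causality judgement. If the rule in the assessor's hands is the strictest one, fewer events reach those classes than the protocol's own definition intends. Centres facing an event that fits neither category would each have to improvise.

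**Working it through.** No arithmetic applies: the document gives no event rates and no figure that depends on relatedness. The check is to run the definitions over the possible situations.

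Take an event with reasonable timing after trial medication. Read the two sentences under *Related* as joint conditions, and vary how plausible the drug and the other causes are.

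| Situation | Adverse reaction by *Definition of AR*? | *Related*? | *Not related*? |
|---|---|---|---|
| A. Drug is a reasonable possibility; no other reasonable cause | Yes | Yes | No |
| B. Drug is a reasonable possibility; another cause is reasonable but not probable | Yes | No | No |
| C. Another cause is probable; drug still cannot be ruled out | Yes | No | Yes |
| D. Drug can be ruled out; another cause is probable | No | No | Yes |

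1. In A and D the definitions agree.
2. In B the event is an adverse reaction but belongs to neither operative category, although the CRF requires a relatedness assessment. The two categories are not exhaustive.
3. In C the event is an adverse reaction and is at the same time classed 'not related'. This is a direct contradiction.
4. The SAR wording does not settle B or C. A reasonable probability is more than a relationship that cannot be ruled out, but less than the absence of any other reasonable cause. A serious event in B or C could be an adverse reaction and yet, depending on the investigator's opinion, not a serious adverse reaction.
5. A SUSAR must first be a serious adverse reaction, so what is lost at step 4 is lost there too.
6. The commitment to follow to resolution or stability is given for related events. An assessor who applies the *Related* rule literally takes B and C out of it.

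A postoperative thrombotic event is typically B or C: surgery and immobility are reasonable explanations, while the drug cannot be excluded.

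**The case against.** A reader might infer that thrombotic events will be under-reported, that they will all be classed unrelated, or that tables of related events by arm will be nearly empty. The document does not support these readings.

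- All adverse events go on the CRF whether or not they are attributed to study medication. The listed vascular and thromboembolic events are safety endpoints without a causality condition, and *Statistical analysis* compares safety endpoints between arms with no relatedness filter. An event judged unrelated is still recorded, counted and compared.
- No analysis by relatedness is planned in the article.
- 'Not related' is not automatic, because it requires that another cause be probable (situation B).
- Some listed events, such as catheter-related phlebitis and data-sheet side effects, have no obvious explanation in the fracture or the operation.

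Two further objections carry weight. First, an event can become a reaction without passing the *Related* rule: the AR definition accepts the judgement of the reporting professional or the sponsor, and the SAR definition rests on the investigator's opinion. A loss of serious adverse reactions and SUSARs is therefore possible, not certain. Still, the sponsor's route is stated for adverse reactions and not in the SAR definition, and having several routes with different thresholds is itself the inconsistency. Second, follow-up does not vanish for other events: follow-up information is to be given as necessary, a patient removed or withdrawn because of an adverse event has an end-of-study assessment and care until stable, and all arms are followed to 60 days after discharge. Only the explicit follow-to-resolution clause is at stake.

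Finally, 'cannot be ruled out', taken literally, would make almost every postoperative event a reaction. That bears on how the fix is worded; it does not remove the conflict.

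**Conclusion.** The concern holds in a limited form. The definitions of adverse reaction, serious adverse reaction, 'related' and 'not related' contradict one another, and the last two leave a gap. The consequence is confined to causality labels and what depends on them: the counts of adverse reactions, serious adverse reactions and SUSARs can be lower than the adverse reaction definition implies, and some events can lose the explicit follow-up to resolution. Capture of events and the between-arm safety comparison are unaffected.

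The number of events concerned cannot be computed from the document. The direction rests on two assumptions: that assessors apply the *Related* rule as written, with both sentences required, and that many postoperative events in this population have a reasonable alternative cause. The contradiction itself needs neither event rates nor outside sources. Nothing here depends on material missing from a condensed article, since all the conflicting definitions are stated in it. It should be corrected, but it does not threaten the trial's main conclusions.

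**What to change.** Reconcile the definitions of adverse reaction, serious adverse reaction, 'related' and 'not related', and the matching CRF item, to one causality threshold. The natural anchor is the one the protocol already uses to define an adverse reaction: at least a reasonable possibility of a causal link. 'Not related' then becomes its complement, no reasonable possibility, so that every event falls in exactly one category. A serious adverse reaction becomes an adverse reaction that is also serious, with no separate threshold. The gloss about ruling out the relationship should be kept consistent with this, so that it is not read as demanding proof of the negative.

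It would help to add one sentence confirming that the by-arm comparison of the listed safety endpoints uses all events regardless of the causality call. This clarifies what the text already implies and changes no analysis.

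The cost is wording in the safety section and on the CRF, plus guidance to assessors. More events will be classed as suspected reactions and need the handling that goes with that. Sample size, endpoints and the planned analyses stay as they are.

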#### Not related

The adverse event is probably produced by the participant's clinical state or by other modes of therapy administered to the participant.

#### Procedures for recording AE

All AEs occurring during the study/or until observed by the investigator or reported by the participant, whether or not attributed to study medication, will be recorded on the CRF. The following information will be recorded: description, date of onset and end date, severity, assessment of relatedness to study medication, other suspect drug or device and action taken. Follow-up information should be provided as necessary.

AEs considered related to the study medication as judged by a medically qualified investigator or the sponsor will be followed until resolution or the event is considered stable. All related AEs that result in a participant's withdrawal from the study or are present at the end of the study, should be followed up until a satisfactory resolution occurs. It will be left to the investigator's clinical judgment whether or not an AE is of sufficient severity to require the participant's removal from treatment. A participant may also voluntarily withdraw from treatment due to what he or she perceives as an intolerable AE. If either of these occurs, the participant must undergo an end of study assessment and be given appropriate care under medical supervision until symptoms cease or the condition becomes stable.

The relationship of AEs to the study medication will be assessed by a medically qualified investigator.

### Quality control and quality assurance

To ensure investigators are following the protocol, complying with regulatory and Good Clinical Practice (GCP) standards, and collecting and reporting quality data, sponsors of clinical trials monitor the progress of clinical trials performed by the investigators during the clinical trial. The core components of monitoring are to ensure patient protection and to validate integrity of the data. Monitoring involves periodic on-site visits by monitors each year for the duration of a study as part of a quality process. Significant findings identified as a result of monitoring are escalated for review by the sponsor who may then be managed as a suspected significant deviation. Risk assessments and evaluations are then conducted. There are circumstances where decisions have to be made with regard to taking remedial actions, which may include notifying regulatory authorities and ethics committees of any significant regulatory and/or GCP requirements. At all times, the safety and rights of subjects are the top priority for the trial sponsor.

The clinical trial monitor or clinical research associate (CRA) will verify that the data have been faithfully transcribed from the medical records of patients to the CRF, keeping the confidentiality of patients according to Spanish data protection law. If the CRA detected a mismatch between the CRF data and medical history, he/she will open a query with discordant data to be reviewed by the investigator or investigating staff. This query should be corrected by the investigating team. It is the responsibility of the CRA to check all the open queries in every monitoring visit, to check if it has been corrected and to document the corrections performed.

The documents constituting the master file of the study will include all the documents established in the Good Clinical Practice (CPMP/ICH/135/95). The investigator will warrant that all the people involved in the study will respect the confidentiality of any information on the subjects of the trial, as well as the protection of their personal character data (according to Spanish Law 15/1999, on Protection of Personal Data, from the 13th of December). The anonymity of the participants in the study will be preserved at all times. Only the main researcher of each center and the coordinator of the study will have access to the personal information of participants.

The study data will be transcribed onto CRF and only include a code assigned to each patient, to provide a patient identification code. Only investigators, pharmacists and nurses in the study and authorized by government agencies, if necessary, will be able to access the medical records of patients according to Spanish law 15/1999, on Personal Data Protection, from the 13^th ^of December. This confidential information will remain the exclusive property of the principal investigator and investigating team, may not be disclosed to others without prior written consent from the investigating coordinator and the other principal investigators and may not be used except for this study.

The information originated during the course of this trial is also considered confidential and only to be used by investigators in relation to the objectives of the study and its development.

In all stages of the trial development, patient confidentiality will be guaranteed under current regulations. Once the consent form is signed, a subject code is assigned as detailed in the previous section. This code will be the only possible identification for the patient in the CRF. The CRF consists of AutoCalc paper (original + copy), and will be guarded at all times in a locked place by the researcher responsible for the inclusion of the patient. When the collection of clinical information and follow-up of the subject is finished, the CRA will take the original pages and leave a copy in the custody of the investigator responsible for the inclusion of the patient. Original documents and copies of CRF have to be preserved for at least 10 years from the close-end of the trial. All CRF data on each subject will be turned into a database using SPSS 18.0 version, which is encrypted and stored on external memory devices, in the custody of the CRA and the clinical trial sponsor.

### Ethic, deontological and regulatory considerations

The Investigator will ensure that this study is conducted in accordance with the principles of the Declaration of Helsinki, ICH Guidelines for Good Clinical Practice and in full conformity with relevant regulations.

The protocol, informed consent form, participant information sheet and any applicable documents will be submitted to an appropriate Ethics Committee (EC) and Regulatory Authority for written approval.

All substantial amendments to the original approved documents will also be sent to an appropriate Ethics Committee (EC) and Regulatory Authority for written approval.

The trial staff will ensure that the participants' anonymity is maintained. The participants will be identified only by a participant ID number on the CRF and any electronic database. All documents will be stored securely and only accessible by trial staff and authorized personnel. The study will comply with the Data Protection Legislation which requires data to be anonymized as soon as it is mandatory to do so.

Once it is established that the patient meets the selection criteria for recruitment and before starting treatment, the investigator is responsible for obtaining signed informed consent of patients participating in the study after having provided appropriate information about objectives, methods, anticipated benefits and potential risks. In the event that the patient is unable to read or to give consent, the legal representative must be present during the informed consent process and the legal representative must sign the consent form to attest that the information contained in the form has been explained and understood accurately and, where appropriate, give consent. The investigator must also explain that patients are completely free to refuse to participate in the study or withdraw at any time for any reason.

## Discussion

Preliminary results of perioperative use of EPO with or without intravenous iron in HF are promising [15,16,21]; however, these results suffer from bias because trials were not randomized and/or blinded. With the present CT we are trying to definitively demonstrate the efficacy, and if possible the cost-effectiveness of this clinical practice.

Human recombinant EPO has already demonstrated benefits in cardiac, cancer, orthopedic, and bloodless surgery. With respect to orthopedic surgery, its positive impact is readily apparent in patients undergoing elective procedures associated with substantial blood loss (those with hemoglobin levels > 10 and ≤13 g/dl, whose risk for transfusion is estimated to exceed 10%) [22,23]. Patients undergoing major orthopedic surgery who receive EPO have a nearly six-fold reduction in allogeneic transfusion risk; this benefit extends to elderly patients undergoing major hip or knee reconstruction, and also to more heterogeneous populations of patients needing total joint arthroplasty or major hip or knee surgery [24-28]. These data point towards the hypothesis of similar benefits in the case of HF due to similarities in the diseases, the clinical, anesthetic, and surgical procedures, and postoperative care. Nevertheless, some differences make HF patients a unique population, and results obtained in the previous trials are difficult to extrapolate to patients with HF.

On the other hand, iron deficiency correction by oral iron intake is always slower than the correction obtained with parenteral formulations [29]. There are some retrospective studies showing positive results with the use of iron sucrose in preventing RCP transfusions in patients with HF [14-16]. The authors pointed out that, once injected in vivo, the iron-carbohydrate complexes are metabolized, the iron is released where it then binds transferrin in the plasma, and the redundant carbohydrate moiety is then cleared via the liver [30]. This treatment option increases the erythropoietic effect (4.5-5.5 times that of basal) of intravenous iron, which lasts 7-10 days, after which the iron is sequestered by the reticuloendothelial system [31]. In addition, the availability of iron sucrose, and iron carboxymaltose, two intravenous iron preparations with much lesser and milder side effects than iron dextran, has renewed the interest in these therapies [17-19,32]. In this regard, the effectiveness of iron carboxymaltose, which has additional advantages with respect to sucrose, in the correction of anemia after orthopedic surgery, postpartum, as well as in other medical conditions such as inflammatory bowel disease, heart failure, or chronic kidney disease [17-19,33,34], has prompted us to assess its safety and efficacy in the present trial.

In conclusion we think that this trial will contribute with evidence about the safety and efficacy of ferric carboxymaltose with or without EPO in preventing RPC transfusions in patients with hip fracture.

